For each dyad, we will obtain IBS values for each 30 second epoch and each ROI pair. We will also compute the average IBS across each 8–10 min phase of the experiment. In total, we will thereby obtain IBS values for each dyad, from each ROI, for the entire phase and for each 30-second epoch within that phase. To best capture the IBS evoked by social interaction, we normalize the values of the social phase by computing a Z-score, i.e., removing the average value of the solo phase and dividing by the standard deviation. This process is repeated for each dyad. To compare the difference between phases, then, we run a general linear model (GLM). Normalized IBS values are entered as the dependent variable with interactive phases (i.e., collaboration and discussion) and the interaction effect of ROIs (six per dyad) as fixed factors. To assess whether the observed neural activity is most likely due to exchanges between the children, as opposed to being primarily driven by the content of the task, we will also generate random pairings by calculating IBS with false dyads (the child's time-series paired to the time-series of another child coming from a different dyad during the same phase). We will create multiple such random pairs to generate the distribution of IBS expected under the null hypothesis (H0) (Nguyen et al., 2021a). The values of the actual real pairs will then be compared to these H0 distributions, thus providing an empirical *p*-value. An example of this analysis is illustrated for the feasibility study in Figure 5B. We will also generate a more conservative intra-pair comparison based on temporally shuffled behavior. In this case, the participants stay the same but the epochs are randomized to generate false dyads (Ayrolles et al., 2021).

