### 6.1 Claim 1: conjunctions of conversational behaviors across modalities better predict IBS

We argue that focusing on a single conversational behavior (such as eye gaze) under-estimates the complex interplay among modalities in their relationship to neural synchrony. To adduce evidence for this claim we will leverage Long Short-Term Memory (LSTM) networks to predict IBS on the basis of temporal sequences of behavioral data (see Table 1 for further details on the behavior types and variables). Since conversational behaviors are likely to lead to IBS with a certain lapse of time, we insert a 1 to 10 second time lag between the sequences of conversational behaviors and the IBS (Chang et al., 2022). The dataset will be structured into sequential behavioral data over time, each associated with a 30-second interval IBS value and normalized through a Min-Max scaling technique, ensuring consistent proportions across all features, while preserving the original distribution of the data.

**Table 1 T1:** Data sheet.

**Level of data type**	**Modality**	**Dyadic status**	**Specific variables**	**Notes**
Conversational Behavior	Verbal	Non-reciprocal	◾Self-disclosure	Number of behaviors per 30 second epoch.
			◾Reference to shared experience	
			◾Praise	
			◾Teasing	
		Reciprocal	◾Mutual self-disclosure	
			◾Mutual reference to shared experience	
			◾Mutual teasing	
	Paraverbal	Non-reciprocal	◾Pitch shift	
			◾Shift in speed of speaking	
			◾Shift in loudness	
		Reciprocal	◾Mutual pitch shift	
			◾Mutual shift in speech rate	
			◾Mutual shift in loudness	
	Nonverbal	Non-reciprocal	◾Smile	
			◾Head nod	
			◾Gaze at other person	
		Reciprocal	◾Mutual smile	
			◾Mutual head nod	
			◾Mutual eye gaze	
Rapport State		Rapport rating (1–7) for each 30 second interval for each dyad		
Educational Performance		Every week	Task 1–3, week (with x = 1–6)	◾Number of hypotheses per weekly 8–10 min read-out
				◾Number of pieces of evidence per 8–10 min weekly read-out
IBS				◾Right hemisphere ROIs

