### 6.3 Claim 3: IBS Granger-causes reciprocal conversational behaviors

While the previous analyses give a sense of the relationship among time courses, they do not illuminate the direction of influence between one time course and another. To that end, we will compute Granger causality (Granger, 1969). Our prior work already shows that rapport Granger-causes increasing entrainment in some conversational behaviors, and particularly in speech rate (Sinha and Cassell, 2015b). It has also been employed to show that dual brain stimulation improves collaborative learning via the mechanism of spontaneous movement synchrony (Pan et al., 2021). Here we seek to understand whether rapport Granger-causes IBS or vice-versa and, subsequently, whether conversational behaviors Granger-cause IBS or vice-versa. Given the slower time scale of fNIRS signals, a relatively large time window will be used. That is, we hypothesize that it might take as long as 5 seconds for one of these phenomena to Granger-cause the other. The Granger causality approach relies on the accuracy of one time series in predicting the future behavior of another time series. In particular, we determine whether time series *A* (e.g., IBS) Granger-causes time series *B* (e.g., rapport or a relevant behavior feature) by assessing whether incorporating past observations of time series *A* in a linear regression model of time series *B* and time series *A* reduces prediction error compared to a model containing only previous observations of time series *B*.

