In recent neuroscience studies, Granger causality has demonstrated the ways in which men in elderly couples Granger-cause competitiveness in their spouses in the first half of a competitive game, while there is no causality in either direction in the latter half of the game (Zhang et al., 2023). In recently-published research, it has been shown that mutual non-verbal behaviors, particularly mutual smiles, laughter, and body movement anticipate and Granger-cause IBS, even in the absence of a specific task (Koul et al., 2023). However, in that experiment participants were *required* to look at one another, and so spontaneous mutual gaze behaviors were not evaluated. In the current work, we compute the pairwise conditional G-causality in both directions. If no causality is evident in either direction, our prior work motivates looking at the causal relationships between the mutual behaviors previously revealed to be influential in rapport-building and IBS (described above). Therefore, in this case, time series *A* and time series *B* will refer to the average IBS value for every 30-second epoch and the rapport values/occurrence of a relevant behavior for each 30-second slice. The statistical significance will then be assessed through an F-test under the null hypothesis that one time series does not Granger-cause the other. This analysis can reveal both unidirectional influences, wherein one time series significantly Granger-causes the other (i.e., one time series tends to lead the other), and bidirectional influence, indicating that both time series Granger-cause one another in a reciprocal manner. Indeed, if past values of the time series *A* help improve the prediction of time series *B*, and at the same time, past values of time series *B* also help improve the prediction of time series *A*, then bidirectional influence is present.

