### 6.6 Claim 6: brain regions evolve with age

We hypothesize that with age we will find more reciprocal conversational behaviors, as children become more able to participate in interpersonal synchrony, and increasingly able to develop abstract shared mental representations with others, leading to greater IBS. We expect to find IBS particularly in the TPJ for the younger age groups and in the PFC in the older age groups (Dumas et al., 2020). In the absence of prior research concerning the development across middle childhood of the neural correlates of social bond formation, we propose to study IBS across the 4 age groups in relationship to the task (solo vs. collaboration vs. discussion). To that end, following Wang et al. (2022), a GLM model will be used to estimate changes in IBS values across ROIs, pairs, and distinct experimental phases. To ensure robust statistical inference, False Discovery Rate (FDR) correction will be implemented. We believe that the identification of developmental dynamics in IBS will provide valuable insights into the critical cognitive processes at play in rapport, and will thus potentially play a role in guiding the design of interventions.

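### Claim 3's Granger F-tests run in both directions with a follow-on search and no stated multiplicity control, and section 3 predicts both directions, so false-positive support is several times more likely than 5%

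*Protocol article*

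**What the plan says.** Section 6.3 sets the question in both directions and for two kinds of series: "Here we seek to understand whether rapport Granger-causes IBS or vice-versa and, subsequently, whether conversational behaviors Granger-cause IBS or vice-versa". The computation follows suit: "In the current work, we compute the pairwise conditional G-causality in both directions". The decision rule is a plain F-test: "The statistical significance will then be assessed through an F-test under the null hypothesis that one time series does not Granger-cause the other". The section then says what may be concluded: "This analysis can reveal both unidirectional influences, wherein one time series significantly Granger-causes the other", and it allows bidirectional influence as well. It also provides for a further search after a null result: "If no causality is evident in either direction, our prior work motivates looking at the causal relationships between the mutual behaviors" previously found influential in rapport-building, and IBS.

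Section 6.3 states no significance level, correction, ROI or phase. The only multiplicity rule in the article is in section 6.6, for Claim 6: "To ensure robust statistical inference, False Discovery Rate (FDR) correction will be implemented".

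Section 3 (Framework) gives two predictions about order in time. Claim 3 there treats IBS as a precondition of successful dyadic behaviour. A later paragraph of the same section expects patterns of dyadic behaviour to be followed by a rise in IBS.

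The IBS quantity is described in two ways. Section 5.2.2 says "For each dyad, we will obtain IBS values for each 30 second epoch and each ROI pair", and shortly afterwards refers to values from each ROI, six per dyad. The IBS row of Table 1, as it reads in the extracted text, lists right-hemisphere ROIs only.

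**The concern.** Claim 3 is one of six claims that section 3 offers as quantitative and testable. Its test needs a rule by which it could fail. Under section 6.3 as written there are many F-tests, two directions that can each be reported, and a second search triggered by a null first step. Because section 3 predicts both orders in time, a chance finding in either direction can be read as agreement with the framework.

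Two features raise the stakes. Sections 1 and 7 say that the results will shape the virtual peer's behaviour, so a chance lead-lag finding could be built into that tool. Section 4.2 plans to analyse and publish the 9–10-year-old dyads first, so the rule has to be settled before that analysis.

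**Working it through.** **The plan's own figures.** The article gives no test count and no family-wise error rate, so there is nothing to reproduce on this point directly. The alpha of 0.05 comes from the sample-size paragraph (section 4.1). That calculation comes close to its stated result if 0.24 is read as Cohen's f with an assumed correlation of 0.5: λ = f²·N·m / (1 + (m−1)ρ) = 0.0576 × 176 × 6 / 3.5 = 17.4, giving power 0.948 at 176 dyads against the stated 0.95. It matters here only as the source of alpha. Applying 0.05 to the F-tests is an assumption.

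**Inputs for the count**
- Reciprocal behaviours in Table 1: 3 verbal (for example "Mutual reference to shared experience"), 3 paraverbal and 3 nonverbal, 9 in all. Rapport makes 10 series.
- Directions: 2 (section 6.3).
- IBS series: not fixed. Three readings are possible: 1 (averaged over ROIs), 3 (right-hemisphere ROIs) or 6 (all ROIs in section 5.2.2).
- One pooled test per series, ROI and direction is assumed. Testing by phase, week or dyad would add tests.

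**Counts:** 10 × 2 × 1 = 20; 10 × 2 × 3 = 60; 10 × 2 × 6 = 120.

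**Formulas, all nulls true.** With independent tests, FWER = 1 − (1 − 0.05)^k. With a common correlation r between two-sided z statistics, FWER = 1 − ∫ φ(u) [Φ((c − √r·u)/√(1−r)) − Φ((−c − √r·u)/√(1−r))]^k du, with c = 1.96, integrated numerically.

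| Tests k | Expected false positives (0.05k) | r = 0 | r = 0.5 | r = 0.8 |
|---|---|---|---|---|
| 20 | 1.0 | 0.64 | 0.42 | 0.22 |
| 60 | 3.0 | 0.95 | 0.66 | 0.31 |
| 120 | 6.0 | 0.998 | 0.81 | 0.38 |

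The smallest entry, 0.22, is about 4.5 times 0.05.

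**Only the direction named in Claim 3.** Counting only IBS to the 9 reciprocal behaviours leaves 9, 27 or 54 tests. At r = 0 down to r = 0.8 the ranges are 0.37 to 0.17, 0.75 to 0.25, and 0.94 to 0.31. Naming the direction alone does not bring the error near 5%.

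**The conditional second step.** Running the mutual behaviours only after a null rapport step does not lower the chance of at least one false positive. With six ROIs and independence, the rapport step has 6 × 2 = 12 tests and the behaviour step 9 × 6 × 2 = 108: 1 − 0.95^12 × 0.95^108 = 0.998, the same as running all 120 together.

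**Effect of a correction.** Bonferroni over 120 tests uses 0.05/120 = 0.000417 per test and gives 1 − (1 − 0.000417)^120 = 0.049 under independence. An FDR rule at 5% also holds the chance of any rejection to 5% when all nulls are true and the tests are independent, and it costs less power when some effects are real.

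**The case against.** The strongest reply is that this rests partly on silence. An article condenses a fuller plan, and significance levels and corrections are commonly left to it. Section 6.3 never says that the F-tests are uncorrected, and requiring FDR for Claim 6 does not exclude it elsewhere. That stands as far as it goes: a fuller plan may add a correction. It does not dispose of the point, because section 6.3 itself fixes the F-test rule, the acceptance of either direction and the follow-on search, and section 3 contains both predictions. Those statements would still need reconciling.

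It can also be said that computing both directions is how Granger analysis separates leading from mutual influence, and that the heading of section 6.3 names a direction. Both are true. Computing both directions is not the fault. The gap is that the section does not say which result supports Claim 3.

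A reader might infer more than the documents support:
- *That 120 tests will be run.* This is a reconstruction. Section 6.3 speaks of an average IBS value per epoch, which could mean one series per dyad. Table 1 suggests three ROIs. The mutual behaviours examined may be fewer than nine.
- *That a false result is almost certain.* That is so only for large counts near independence. At r = 0.8 even 120 tests give 0.38.
- *That the same applies to Claim 2 and to the comparison of real with false pairs.* Section 6.2 sets a permutation test and an ANOVA and leaves the level open. Section 5.2.2 promises an empirical p-value without saying that there is one per ROI and phase, and its example figure covers the right TPJ only.
- *That a single right-TPJ contrast is needed.* The pilot support is five dyads, which section 10 calls too few for conclusions, and Claim 6 predicts a shift from right TPJ towards PFC with age.

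**Conclusion.** The point holds in this form. Section 6.3 sets F-tests in both directions, for rapport and then behaviours, with either direction reportable, a further search after a null first step and no stated error control, while section 3 predicts both orders. Followed as written, the chance of at least one false Granger result is about 0.22–0.64 for 20 tests, 0.31–0.95 for 60 and 0.38–0.998 for 120, which is several times the nominal 0.05 under each of these counts. The figures assume 0.05 per test, one pooled test per series, ROI and direction, all nulls true, and a common correlation between 0 and 0.8. The exact rate cannot be fixed because the number of tests is not stated. A correction in an analysis plan not shown would remove the inflation but not the conflict between the two predictions.

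**What to change.** 1. In section 3, reconcile the two statements on whether IBS precedes or follows reciprocal behaviour.
2. In section 6.3, state that only IBS-to-reciprocal-behaviour results support Claim 3, and that the reverse direction is reported as secondary.
3. Extend the FDR rule of section 6.6 to the whole set of Granger tests (ROI × behaviour × direction × phase), including the conditional second step, and state the level.
4. In section 5.2.2, state whether the tested IBS values are the six homologous ROIs or all ROI pairs. Apply the same FDR rule to the real-versus-false-pair p-values if these are computed for more than one ROI or phase.

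No single ROI or phase need be prescribed. The change is to wording only, needs no new data, and should be made before the 9–10-year-old data are analysed. The cost is that some nominally significant ROI or behaviour results will no longer count.

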### 6.4 Claim 4: not all rapport is productive: adding in performance data

While rapport is often seen as beneficial in general, and in particular for collaborative tasks, its impact on task performance is not uniformly positive. To investigate this, we propose integrating performance data into our analysis of IBS, conversational behaviors, and rapport. Methodologically, we will first compute the specific performance metrics relevant to the tasks undertaken by dyads in our study, as described above. In order to associate these metrics to conversational behaviors, rapport level, and IBS, over time, we count the number of hypotheses, and evidence statements supporting those hypotheses, in the read-out session between the children and the experimenter for each week, and we associate these performance metrics to the rapport utopy score for that week, and the mean IBS score for the collaboration phase for that week. Our hypothesis is that while a moderate level of rapport is likely to be beneficial for performance, either too little or too much rapport might hinder task effectiveness. This could be due to an overemphasis on maintaining harmonious interactions at the expense of task focus, or conversely, insufficient rapport leading to poor collaboration. We therefore expect to find a non-linear relationship, potentially inverted U-shaped, between rapport levels and task performance. To test this hypothesis we will employ regression models, including quadratic regression, to test the hypothesized inverted U-shaped relationship. This will enable us to assess the impact of varying levels of rapport on performance metrics while controlling for other variables. Furthermore, we will conduct subgroup analyses to explore if this relationship varies across different dyads, tasks, levels of IBS or ages, or over the 6 weeks of the study. This could involve stratifying dyads based on one of these variables. By integrating performance data, we aim to provide a more nuanced understanding of the role of rapport in collaborative tasks. This kind of analysis may be supplemented by machine learning models such as random forests, where the model is trained on a portion of the data, with the random forests constructing multiple decision trees during the training, and outputting the mean prediction of these trees. In essence this enables the model to recognize complex patterns, such as how different variables interact to affect task performance, thus potentially uncovering intricate relationships such as the hypothesized non-linear relationship between conversational behavior, rapport, and task performance. Techniques of this sort, however, require a significant amount of data as, after training, the model is validated on a separate dataset to assess accuracy. If 176 dyads are collected, the amount of data could be sufficient. The results could have important implications for how rapport is fostered in team settings, particularly in educational and organizational contexts, where performance outcomes are critical. The insights gained from this analysis could contribute to a more comprehensive model of interpersonal dynamics, extending beyond the simple premise that more rapport is always more beneficial.

### 6.5 Claim 5: rapport-building is a process that takes time

We will employ Dynamic Network Analysis (DNA) as the simplest way to address Claim 5′s exploration of the longitudinal interplay between IBS and rapport over the course of 6 weeks. In this analysis, each dyad will be represented as a network, with nodes denoting sensors and edges indicating the strength of IBS. The temporal alignment of these networks will ensure uniformity across different time points, enabling a consistent examination of changes in connectivity. Employing dynamic network metrics, including variations in edge weights, will facilitate a comprehensive capture of evolving patterns in dyadic interactions. Visualization techniques, such as animations, will be employed to enhance the intuitive comprehension of temporal dynamics within these networks. Rigorous statistical analyses will involve comparing metrics across different time points and identifying relationships between those changes in network patterns and the evolution of rapport.

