
At the intersection of cognitive science and neuroscience lie experiments that deploy the tools of each to both better understand and better support human social interaction in all its complexity. We specifically argue here that a better understanding of the neurobiological basis of social interaction between children is necessary, including how the building of social bonds with peers develops over the course of multiple interactions, and over middle childhood. Since learning is the primary “job” of children, as a part of this investigation we also examine how certain types of rapport may increase learning while others may be detrimental. These topics require a dyadic perspective of the kind described above, as well as a perspective that implicates multiple levels of data—conversational, psychological, and neurobiological, as well as multiple approaches to understanding their conjunction. As hyperscanning research has progressed and continues to grow rapidly (for reviews, see Babiloni and Astolfi, 2014; Czeszumski et al., 2020), including through the use of fNIRS (Pinti et al., 2018, 2020; von Lühmann et al., 2021), it has become possible to evaluate theories concerning the nature of social interaction through *in-situ* experimentation by enabling the concurrent examination of multiple brains. This is achieved through the measurement of IBS, which assesses the temporal coherence and/or consistency in phase and amplitude of neural or hemodynamic signals across a specified time period (Dumas et al., 2010). The advances in electroencephalography (EEG) and fNIRS hyperscanning have allowed recent studies to more directly address the neural signature of social interaction, including a number of studies looking at conversational behaviors. Jiang et al. (2012) found that IBS was more present in the left inferior frontal cortex during face-to-face dialogue than when sitting back-to-back, suggesting a role for non-verbal behavior. More recently, mutual eye gaze has been identified as a potential modulator of IBS in several studies (*inter alia;* Dikker et al., 2017; Cañigueral and Hamilton, 2019; Piazza et al., 2020). Kinreich et al. (2017) report the first hyperscanning study integrating detailed annotation of non-verbal behaviors—what they call gaze and positive affect. They found that IBS was present in romantic couple dyads and not stranger dyads, and that gaze was positively correlated with IBS, while expressions of positive affect were weakly correlated, with no effect found for speech content. However, affects are underlying psychological states, and are themselves correlated with a number of different observable non-verbal behaviors, which may have therefore obscured a correlation. In addition, content of speech was not defined, and specific functions of talk may be more related to IBS than others, as described above. This is also suggested by Nguyen et al. (2021b) where an fNIRS hyperscanning protocol examined free discussion between pre-school children and their mothers. Turn-taking, conversational relevance and content contingency were assessed and only the number of turn-taking instances was correlated with IBS. This study is one of few that examine the temporal dynamics of IBS. Results showed that IBS increased more over time in mother-child dyads than in random pairs, and increased turn-taking throughout the 4-min conversation was associated with greater IBS later in the conversation. However, the presence of silences was used to assess turn-taking, while research has shown that non-verbal behaviors such as eye gaze also play an essential role (Kendrick et al., 2023), and that turn-taking can include significant overlap in speech, as well as silences. For an informative review of studies such as these, see Kelsen et al. (2022).

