### 4.2 Task description

Adducing evidence for the claims outlined above places a number of constraints on the kind of task we can use: in order to investigate neural synchrony during collaboration, the task must allow both a solo and collaborative mode, so that we can compare IBS between the two and ensure that it is not due to looking at the same stimuli (Hasson et al., 2008). The task also needs to encourage social exchange, as well as to be engaging for children in a quite wide age-range (5–12 years old). In order to measure performance, the task must have answers–either tasks with correct answers, or where the nature of answers can be assessed. The age of the participants indicates that they will have a relatively short attention span, meaning that the task must be able to be completed relatively rapidly. On the other hand, since a relatively rapid task may not give enough time for rapport to develop, we have designed a longitudinal component, whereby participants engage in slightly different but comparable tasks, spending 2 weeks on each of three tasks, for a total of 6 weeks, as we have done in prior research (Finkelstein, 2018; Madaio et al., 2018; Cassell, 2022). In order to collect high-fidelity data, the task needs to be displayed on the external screen in front of the child (rather than on a piece of cardboard laid on a table, for example) so that the child's face and body are oriented toward a webcam and microphone placed next to the monitor (the computer and keyboard will be located elsewhere to diminish distractions). Finally, because a subsequent study will integrate an AI learning companion that is based on optimal performance in the child-child task, the task must allow a virtual peer agent to collaborate with the child, as well as allowing two real children to participate.

Keeping all of these constraints in mind, we therefore designed a relatively simple paradigm: a set of three tasks (described below) that ask children to generate hypotheses and evidence for their hypotheses. The children work on each of the three tasks for 2 weeks, meaning that the entire study takes 6 weeks.

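### Section 6.5 judges change in IBS networks over the six weeks with no reference for change, so week-to-week change shared by all dyads could pass as partner-specific

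*Protocol article*

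**What the plan says.** Section 6.5 (Claim 5) proposes dynamic network analysis: "each dyad will be represented as a network, with nodes denoting sensors and edges indicating the strength of IBS". On inference it says "Rigorous statistical analyses will involve comparing metrics across different time points", with the network changes then related to how rapport develops. No false-pair, solo-phase or other yardstick for change is named there.

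Section 5.2.2 plans false dyads, formed from "the child's time-series paired to the time-series of another child coming from a different dyad during the same phase". Week is not part of the matching. Their use is stated: "The values of the actual real pairs will then be compared to these H0 distributions, thus providing an empirical *p*-value". An epoch-shuffled version within real pairs is added. The same section z-scores social-phase IBS against the solo phase for each dyad and enters normalised values for both interactive phases in a GLM. It does not say whether the normalisation is redone each week or carried into the sensor-level networks of 6.5.

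Section 4.2 gives every dyad the same order of tasks: imaginary animal in weeks 1 and 2, bridge in weeks 3 and 4, ramp in weeks 5 and 6. It justifies the solo mode thus: "so that we can compare IBS between the two and ensure that it is not due to looking at the same stimuli".

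Section 2 reports from a cited time-course study that "IBS increased more over time in mother-child dyads than in random pairs". Section 5.2.1 cites the same study for its 30-second epochs.

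**The concern.** A test of IBS level and a test of IBS change answer different questions. Real pairs can exceed false pairs in all six weeks while both change by the same amount. The section 5.2.2 comparison would then succeed every week, yet the week-to-week change would say nothing about the partner.

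Shared change is likely by design. A week 1 versus week 6 difference is also an animal-task versus ramp-task difference in every dyad. Habituation to the cap and room could add to it, though the argument does not need it.

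At stake is the neural part of Claim 5, that is, whether a change in network metrics can be attributed to the interaction of these two children. The link to rapport is exposed in one case: if weekly values are pooled and both series trend over the same weeks, a common trend produces an association.

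**Working it through.** **Inputs from the article.** 176 dyads, alpha 0.05, 44 dyads per age group (section 4.1). The 9–10-year-olds are to be analysed and published first (section 4.2), so 44 is also a relevant size.

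**Inputs assumed.** The size of the shared drift (in SDs of a weekly IBS metric), a within-dyad correlation of 0.5 between weeks, and a paired week 1 versus week 6 comparison. The article gives none of these.

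**The plan's own figure.** For a between-group test in a repeated-measures ANOVA, λ = N·f²·m/(1+(m−1)ρ). With N = 176, f = 0.24, m = 6, ρ = 0.5: λ = 176 × 0.0576 × 6/3.5 = 17.4, and power with 4 groups is 0.948. The first multiple of four to reach 0.95 is 180. So 176 reproduces closely if 0.24 is Cohen's f and ρ is 0.5. The point here uses 176 only as a sample size.

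**Step 1: raw change in real dyads, no partner-specific effect.** SD of change = √(2(1−0.5)) = 1 weekly SD. Noncentrality = drift × √n, with √176 = 13.27 and √44 = 6.63. Two-sided rejection from the noncentral t:

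| Shared drift (SD) | 176 dyads | 44 dyads |
|---|---|---|
| 0 | 5.0% | 5.0% |
| 0.1 | 26.1% | 9.9% |
| 0.2 | 75.1% | 25.4% |
| 0.3 | 97.7% | 49.4% |
| 0.5 | about 100% | 90.0% |

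For example, 0.2 × 13.27 = 2.65 gives 75.1%, and 0.3 × 13.27 = 3.98 gives 97.7%.

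**Step 2: the same test with a reference for change.** Simulation, 4,000 replicates, no partner-specific effect. The false-pair average carries the shared drift plus noise of SD 0.1. Solo-phase error is half that of the interactive phase. The solo reference is a same-week subtraction. Rejection rates:

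| Dyads | Drift | Raw | Solo reference | False-pair reference |
|---|---|---|---|---|
| 176 | none | 4.4% | 4.1% | 4.6% |
| 176 | 0.3, all phases | 97.5% | 4.8% | 4.7% |
| 176 | 0.3, interactive phases only | 97.8% | 94.4% | 4.4% |
| 44 | 0.3, all phases | 49.2% | 4.8% | 5.2% |
| 44 | 0.3, interactive phases only | 48.9% | 41.3% | 5.8% |

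A weekly solo reference therefore removes drift common to all phases, but not drift confined to the interactive phases. The false-pair reference holds in both cases because the drift was simulated as equal in real and false pairs.

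**Step 3: the rapport link.** In the same simulations rapport change rose by 0.3 SD on average, independently of IBS change. The between-dyad correlation of the two changes was significant in 4.8% to 5.2% of runs across all settings. A drift common to all dyads does not bias that form of the test.

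**The case against.** The strongest reply is that section 6.5 is a short outline in a condensed article, and a reference distribution for one exploratory analysis may sit in a fuller plan. Silence is not a statement that only real dyads will be used, and nothing in 5.2.2 bars false dyads from 6.5. That stands in part. However, 6.5 does state which comparison bears on Claim 5, and that comparison alone cannot separate shared from partner-specific change. Sections 6.2 and 6.3, in the same article, do name their null references (a permutation test and an F-test).

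Second, the solo-phase z-score is a real safeguard. Section 3 says each session has a solo phase, so a same-week reference exists. If applied weekly, it would remove drift common to all phases, plausibly including habituation to the cap and room. This stands, but the article does not say that it is applied weekly or to network edges, and it leaves drift limited to interactive phases.

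Third, a reader might infer that any shared drift will be read as a growing bond. The article does not support that. Claim 5 concerns the time course of rapport and predicts no rise in IBS over weeks, and section 2 cites work in which IBS fell as cooperation rose. A reader might also infer that drift necessarily creates an association with rapport. It does so only if trending weekly series are pooled, and 6.5 specifies no such model.

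Fourth, the cited random-pair contrast was made within a 4-minute conversation, not over weeks. The logic carries over, but the precedent is not exact. Finally, false pairs cannot remove task-driven change in real interaction itself. If the ramp task prompts more exchange than the animal task, real-pair IBS may change more than false-pair IBS with no change in the relationship. This stands and limits what the fix can deliver.

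**Conclusion.** The point holds in a limited form. Section 6.5 names no reference for change over the six weeks, and the false dyads of 5.2.2 address presence of IBS, not its change. Change shared across dyads and not removed by solo-phase normalisation could therefore be taken as change in the dyads' interaction.

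The size is illustrative. With 176 dyads, a shared drift of 0.2 or 0.3 SD would be declared significant in about 75% or 98% of studies, against about 5% with a false-pair reference. With 44 dyads the raw figures are about 25% and 49%. They rest on assumed drift, a within-dyad correlation of 0.5, a paired week 1 versus week 6 test, and drift equal in real and false pairs. The article neither reports such drift nor says that it would be read as a strengthening bond. The change is worth making because it is cheap and gives a less biased test, and the article itself reports the same kind of contrast from a study it cites.

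**What to change.** In section 6.5:

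- Compute the same network metrics for false dyads re-paired within the same week, task, phase and age group. Test the week effect as pair type by week (real minus false).
- Compute network edges from IBS normalised to the same week's solo phase, and say so.
- Test the link to rapport as a between-dyad association of IBS change with rapport change, or against re-pairings of one dyad's rapport with another dyad's IBS. Do not pool trending weekly series.
- Describe week-to-week IBS change as partner-specific only if it differs from false-pair change. State that task order remains confounded with week.

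The cost is a few sentences, compute time and slightly wider intervals. False dyads are already planned under 5.2.2, and no new data are needed.
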